#### Dose

The proposed IYP will be administered twice a week for 1.5 hours duration per session for 6 weeks. The length of the IYP, class duration, and number of sessions was based on our previous research using IY for young populations. We found significant effects after a 5-week biweekly (90-minute sessions) IYP for depression in young adults. However, these participants did not have clinical levels of depression or a chronic condition, and a longer intervention is appropriate for the present patient population. Most recently, we conducted a pilot study of a 6-week biweekly (90-minute classes) IYP for young adults with RA [82] and found significant reductions in pain and symptoms. It was therefore deemed suitable to strive for the maximum benefit in the shortest time likely to achieve benefit (6 weeks). The weekly monitoring form (described below) will track symptoms over the study period and help to further inform studies about appropriate dose for young people.

#### Yoga adherence monitoring board

A board will be created with the purpose of monitoring instructor adherence to the study manual. The board will consist of two senior IY teachers, who will conduct ratings for teacher adherence by reviewing notes from the classes. A research assistant will attend a random selection of 25% of classes to note poses completed, use of props, and any modifications or difficulties experienced. Using a checklist, the board will rate the extent of adherence to the yoga manual.

### Laboratory pain task

The following task designed to measure visceral sensitivity will be administered in the PPP laboratory both at baseline and then post-intervention following the IY intervention/control groups.

#### Water load task

(WLT) to assess visceral sensitivity. Visceral sensitivity tasks are designed to challenge patients for sensitivity to visceral sensations. Walker and colleagues [83-85] developed the Water Load Pain task, which creates visceral sensations similar to pain episodes in children with abdominal pain. Water is administered orally as a single trial of visceral sensation of abdominal discomfort. This task correlates with the threshold for pain/discomfort measured using an electronic barostat and has been shown to be safe in healthy and clinical samples of adults and children; and it is far less intrusive than other measures of visceral sensitivity, such as rectal distension [86,87]. After a two-hour fast, subjects will be asked to drink non-caloric, non-carbonated filtered water at room temperature in as large a quantity as possible until s/he feels completely full or reaches a limit of intolerability with an uninformed ceiling of 15 minutes. Subjects will be informed that this is 'not a race.' Subjects will be blinded as to the total volume ingested. The time (seconds) elapsed from the beginning of water ingestion until the subject stops drinking will be recorded.

#### Measures

*To assess the outcomes and mediators depicted in the conceptual model (Figure*1)

## Primary outcomes

### Questionnaires at baseline, post-treatment, and follow-up

**1**. ***IBS symptoms ***will be measured using the ***IBS severity scoring system (IBS-SSS) ***[88]. The scale measures the sum of the participant's evaluation on a 100-point scale of each of five items: severity of abdominal pain, frequency of abdominal pain, severity of abdominal distension, dissatisfaction with bowel habits, and interference with quality of life. The IBS-SSS has acceptable reliability and validity and is recommended for use in outcome studies [89]. It takes approximately 5 minutes to complete. Those younger than 18 will also receive the abdominal symptoms sub-scale of the Child Somatization Inventory (CSI). The CSI [90-93] measures perceptions of nonspecific somatic symptoms. Individuals rate how much they are bothered by each of 24 symptoms (e.g., headaches) during the last 2 weeks using a 5-point scale (*not at all *to *a whole lot*). It takes less than 5 minutes to complete.

**2. *IBS pain ***will be measured with the ***Abdominal Pain Index ***comprising five items assessing the frequency, duration and intensity of pain episodes over the previous 2 weeks. Good reliability and validity have been reported [94].

**3**. ***Global Improvement ***will be assessed with the ***Global Improvement Scale **(**GIS**)*. This scale asks participants "Compared to the way you felt before you entered the study, have your IBS symptoms over the past 7 days been from (1) = substantially worse, to (7) = substantially improved [95]". Global improvement is noted for patients endorsing moderately or substantially improved status. The scale shows adequate reliability and validity [95]. Global improvement, in addition to symptom severity, is recommended as a primary endpoint in IBS therapy trials [96]. The scale takes less than 1 minute to complete.

**4**. ***Health Related Quality of Life ***will be assessed with the ***Health Related Quality of Life - Short Form-36 (SF-36) ***[97] a generic core HRQOL measure yielding an 8-scale profile of functional health and well-being. The SF-36 performs well in an absolute sense and comparatively better than other HRQOL measures in terms of reliability, validity, and lightness of respondent/administrative burden [98]. It can be completed in 5-10 minutes and has been validated in children as young as 10 years of age [99].

#### Secondary outcomes

**1. *Functional Disability Index (FDI) ***[92] is a 15-item measure assessing perceived difficulty in physical and psychosocial functioning in the past 2 weeks due to physical health. Items are rated on a 5-point scale (*no trouble *to *impossible)*. It takes less than 5 minutes to complete.

**2**. ***Visceral Sensitivity Index (VSI) ***is a reliable, valid measure of gastrointestinal symptom-specific anxiety [100]. It has 15 items assessing anxiety related to gastrointestinal sensations that are rated on a 6- point scale from *strongly agree *to *strongly disagree *and takes less than 5 minutes to complete.

3. *Laboratory assessment at baseline and post-treatment*

**Visceral pain sensitivity **will be assessed via the **water load task**, a measure of visceral pain. Laboratory pain tasks provide a standardized, controlled way of assessing pain sensitivity. The laboratory procedure will take approximately 30 minutes.

##### Self-report and behavioral pain sensitivity

1. Pain Intensity: Self-report ratings of pain intensity will be recorded on a 10 cm vertical visual analog scale (VAS) used to represent a continuum from *no pain at all *to *worst pain imaginable*. The VAS has been widely used as a valid and reliable measure of pain intensity with children [101] in experimental and clinical pain studies.

2. Pain Tolerance: Maximal water intake (mL), adjusted for BMI, will be recorded. Tolerance represents a behavioral measure of pain response.

3. Pain Discomfort: Subjects will be asked to rate their discomfort using the VAS to represent a continuum from *no discomfort at all *to *worst discomfort imaginable*. The measure will assess the affective component of the pain. Participants will be asked 'how much does your stomach feel bad or uncomfortable?'

4. Anticipatory Anxiety: Before each pain task, subjects will use the vertical VAS automated slider to rate how anxious or nervous they are about performing the upcoming task, in response to the question 'how nervous, afraid or worried are you about the task?'

5. GI and Non-GI Symptoms: The Symptom Emotion Report is a 21-item measure developed by [name] lab that measures GI (e.g., nausea/upset stomach) and non-GI (e.g., tired, upset) symptoms experienced immediately before and after the WLT on a 5-point numerical scale of 0 (*Not At All*) to 4 (*A Whole Lot*). Williams et al. [102] found that GI symptoms reported during abdominal pain episodes significantly predicted GI symptoms experienced following the WLT.

#### Psychospiritual functioning

**1. *Self-efficacy ***will be assessed with the ***Pain Self-Efficacy Questionnaire (PSEQ) ***[103], a brief self-report of self-efficacy for functioning despite chronic pain. The scale consists of 10 items, takes 2 minutes to complete, and asks about functioning when in pain; functioning domains include activities related to school, friends, family and work (including household chores). Acceptable reliability and validity have been reported [103].

**2. *Pain Catastrophizing ***will be assessed with the ***Pain Catastrophizing Scale (PCS) ***[104] a 13-item self-report instrument based on the catastrophizing subscale of the Coping Strategies Questionnaire [105]. Respondents select one of five response options (*not at all *to *all the time) *indicating the degree to which they experience each item (i.e. "When I'm in pain, it's terrible and I think that it is never going to get any better"). This measure takes less than 5 minutes to complete.

**3**. ***Mood ***will be evaluated using the ***Brief Symptom Inventory 18 (BSI-18) ***[106]. Respondents rate how often they have experienced anxiety, somatization, and depressive symptoms within the past 7 days on a 5-point scale ranging from *not at all *to *extremely*. The BSI-18 has shown adequate to good internal consistency (α range = .74 - .89) and validity [106]. The BSI-18 requires a 6^th ^grade reading ability and takes approximately 5 minutes to complete. Children under 18 years will be administered the Revised Child Anxiety and Depression Scale (RCADS) [RCADS; [107,108]], a 47-item adaptation of the Spence Children's Anxiety Scale (SCAS) [SCAS; [109,110]]. This measure assesses children's report of symptoms corresponding to selected DSM-IV anxiety disorders and depression. This measure takes 10 minutes to complete.

**4. **The ***Chronic Pain Acceptance Questionnaire (CPAQ) ***[111] is a 20-item measure to assess acceptance of chronic pain. The CPAQ has two subscales: Activity Engagement assessing patients' participation in activities regardless of pain and Pain Willingness, assessing absence of attempts to control or avoid pain. The CPAQ has acceptable reliability (*α *= .78-.82) and validity [111]. It takes approximately 5-10 minutes to complete and is suitable for older adolescents as young as 16 years of age.

**5. *Mindfulness ***will be assessed using the ***Mindfulness Attention Awareness Scale (MAAS) ***[76], a 15-item measure rated on a 6-point Likert scale. Internal consistency is high (α = .82) and the scale has acceptable convergent and discriminant validity [76]. The scale has been used with adolescents and young adults [112] and was initially developed with participants aged 17 years and above. It takes approximately 5 minutes to complete.

### Exploratory mediators

#### Laboratory physiological responses at baseline and post-treatment

##### Physiological responses

Noxious stimuli such as pain or emotional distress are known to activate the neuro-hormonal stress response [113]. The stress response is modulated primarily by corticotropin releasing hormone (CRH) and the autonomic nervous system. Pain has been shown to activate the hypothalamus (hormonal response) and the periaqueductal gray (autonomic nervous center) [114]. The overall physiologic expression of the stress response is manifested from a balance between hormonal influences, sympathetic tone, and parasympathetic tone. The acute stress response is characterized by increase in heart rate, blood pressure, respiratory rate, skin conductance, and cortisol.

##### Autonomic responses

Autonomic arousal will be determined from measures of skin conductance, heart period, respirations, and blood pressure recorded continuously during the lab sessions using a BIOPAC MP150 recording system (BIOPAC, Inc., Santa Barbara CA). Briefly, skin conductance (SC), which reflects peripheral sympathetic activity, is recorded using Ag/AgCl electrodes secured to the volar surface of the first and third fingers of the non-dominant hand. Heart period (HR) is recorded using a two lead ECG from electrodes attached to the jugular notch and over a lower rib. HR and SC are sampled at 1000 hz and analysis of skin conductance level, skin conductance responses, average HR, and heart rate response during each task is computed using BIOPAC software (for peak detection and averages) and specialized software developed in our laboratories over the past 10 years. Blood pressure is recorded using a noninvasive system supplied by BIOPAC (NIBP100A), which records radial artery waveform from a non-occluding wrist cuff. Using a patented algorithm the NIBP100A system calculates accurate systolic, diastolic, and mean pressures and has been validated against arterial recordings. Respiration is recorded using an abdominal belt and used to check for unusual breathing patterns that might impact interpretation of the other measures. Heart rate variability (HRV) is determined from the interbeat intervals using specialized spectral analysis software developed for this purpose [115,116], which produces separate area and peak power measurements for the low frequency (parasympathetic and sympathetic influences) and high frequency (parasympathetic or vagal) components of heart period. Heart rate variability will be assessed by including a measure of respiration (to calculate respiratory sinus arrhythmia). Boyce and colleagues [117] have established the reliability and validity of this system for physiological recording in children as young as 3. Cardiac vagal tone is also estimated using a software filter to detect respiratory sinus arrhythmia (RSA, Delta-Biometrics, Bethesda, MD). RSA is the normal variation in heart rate occurring in synchrony with the inspiratory and expiratory phases of the respiratory cycle. ANS variables will include resting and maximum change values during each task for: blood pressure, skin conductance, high frequency HRV (vagal tone), and sympathetic balance (HF/LF).

##### Cortisol

Salivary cortisol, a neuroendocrine marker of HPA axis reactivity has long been used in the study of the psychobiology of stress [118]. Salivary cortisol will be used as a physiological evaluation of general stress, and whether patients' stress response changes as a result of the IYP. Collection of cortisol through saliva is a non-invasive way of measuring HPA axis activity and is correlated with unbound serum levels [119]. Fifteen minutes prior to the first collection, participants will be asked to rinse their mouth with water to prevent contamination of sample by food debris. Subjects will also be instructed not to eat or drink 1 hour prior to the session to minimize sample contamination. Participants will be instructed to imagine smelling and eating their favorite food and to begin to allow the saliva to pool at the bottom of their mouths. Saliva samples will be collected with small straws placed in the mouth so that the saliva can easily be collected into a cryovial. We will aim to collect 1.5 mL of saliva at each collection from each participant. Saliva is then frozen and sent to the UCLA CNS Endocrine Core laboratory for quantification. Salivary cortisol will be collected before and after each laboratory session as well as the morning of the laboratory assessments. Each laboratory session will involve three samples: immediately upon arrival (initial baseline measure); directly after completing the questionnaires (second baseline measure); and 20 minutes after the end of the visceral sensitivity task (maximal stress response). A meta-analysis of acute psychological stress reveals that the overall peak cortisol response occurs 21-40 minutes from onset of an acute stressor level [120]. One of the most prominent features in studies of adrenocortical responses under physical and psychological stimulation is the large variation in both baseline levels and in response magnitude between subjects. We intend to assess salivary cortisol twice before the pain tasks to control for individual differences at baseline and to capture the possible effects of anticipatory stress on cortisol elevation. These multiple assessments should reflect the overall magnitude of cortisol changes [121].

### Additional measures

**1**. An **expectation **question will be administered after assignment and before treatment to assess whether treatment expectation impacts outcomes. Subjects will be asked to rate on a scale of 0 to 10 'How much do you think the treatment will benefit you or improve your IBS symptoms?'

**2**. The **weekly monitoring form **will include items related to mood, IBS pain, symptoms and functioning and use of any new interventions. The form will be administered by telephone or e-mail at the end of each week to both groups. The weekly monitoring form is an important tool in the study design, given that IBS is a condition without clear biomarkers to assess illness severity and progression, self-reported pain, symptom and functioning tools will form the basis for assessment of appropriate dose. The form will also ensure the control group does not introduce any new mind-body treatments during the intervention.

**3**. Females will receive a question that asks about their last menstrual period (LMP) to control for potential varying pain sensitivity over cycle phase. Self-reported menstrual cycle length is a common, non-invasive clinical marker for reproductive function [122].

Participant Burden: It is anticipated that the laboratory procedure and the standardized questionnaires will take 1.5 hours at baseline, and 1.5 hours post-treatment. The 2-month follow-up is expected to take 40 minutes. The weekly monitoring form will take approximately 8-10 minutes each week.

### Data management

A unique ID will be assigned to each patient for the purpose of protecting anonymity, and no patient identifiers will be included in the dataset. Data from the standardized quantitative measures will be entered into an Excel database then moved into SPSS, which will be used for the statistical analyses. Initial data cleaning and preparation will include evaluation of the distributions, outlier/error detection, logical and range checking and creation of derived variables. Sensitivity analyses will be conducted after imputing for missing data.

### Data analyses

Each stage of data analysis detailed below will be carried out separately for adolescent (14-18 yrs) and young adult (19-26 yrs) sub-groups. If no differences are found, the groups will be combined. It is unlikely that differences will emerge in terms of feasibility, efficacy or safety, but a separate analysis of sub-groups will ensure that findings are generalizable across the ages studied.

Once the data set has been cleaned and examined for skewness, exploratory data analyses will be conducted using univariate methods to describe the variables of interest and bivariate techniques to characterize their interrelationships within our sample. Continuous variables will be summarized over time in each group using means, medians, range, interquartile range and standard deviations. Cross tabulated frequencies will be given for all discrete variables by group and time. Both parametric and non-parametric correlations will be reported. Expectation ratings will be correlated with primary outcomes to determine whether patient expectations were related to post-intervention symptoms.

For **Hypothesis 1**: IY will be safe, acceptable and feasible: more than 80% of subjects will complete the training program, the frequencies of drop-outs for the IYP and control groups will be examined. Attrition rates will be compared between the yoga and control groups; demographics and baseline values of functioning between those who complete the protocol and those who do not will also be compared. If drop-outs are random, then the results may be considered unbiased. If drop-outs are not random, the direction and magnitude of potential biases will be considered.

To test **Hypothesis 2: **Participants in the IY group will demonstrate significantly greater improvement in IBS symptoms, global improvement and HRQOL apparent immediately post-intervention and at the 2- month follow-up. Consistent with recommendations regarding analyses for randomized trials, analysis of covariance (ANCOVA) will be used to test group differences [123]. The baseline scores of the outcome variables will be entered as independent variables. The Next, analyses will assess maintenance of treatment gains during the follow-up period. Changes in IBS symptoms, HRQOL and improvement across baseline, post-treatment and follow-up will be evaluated using ANCOVAS. An intent-to-treat (ITT) analysis on the primary outcome measures will be conducted to confirm findings in treatment completers by including all participants who enrolled in the study, using the last observation carry forward approach. Even if significant differences are noted, consideration will be given to established minimally clinically significant differences on outcome measures between the groups. Thus, in order to be considered a clinically meaningful difference, participants must evidence a decrease in at least 50 points on the IBS-SSS in comparison to controls.

To test **Hypothesis 3: **Participants in the IY group will report significantly reduced visceral sensitivity, disability and improved psychospiritual functioning. The same methods will be used as described above for hypothesis 2. Similar analysis will be conducted to examine changes in visceral sensitivity, disability and psychospiritual functioning, including self-efficacy, coping, mood, acceptance and mindfulness from baseline to post-treatment.

To test **Hypothesis 4: **As depicted in Figure1, Psycho-spiritual-physiological outcomes will be explored as mediators of the association between IY and improved IBS outcomes. Regression analyses will be conducted to determine whether these variables mediate treatment outcome. The procedures outlined in Cohen and Cohen [124] will be used to calculate residualized change scores for IBS symptoms, global improvement, HRQOL and pain sensitivity scores. Multiple regression analysis will then be conducted with IBS symptoms, global improvement, and HRQOL separately; change scores (baseline minus post-treatment) will be regressed onto a set of predictor variables including group (yoga vs. control), the mediator variable of interest (e.g., self-efficacy), and the interaction between the mediator and group. If evidence of mediation is found using the traditional Baron and Kenny approach - the Sobel test - a statistical test for mediation will be conducted to calculate mediation. Finally, exploratory analyses will be conducted from the Weekly Monitoring data.

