Other strengths of the study include the testing of psychophysiological mechanisms of action based on our published model of yoga (see figure 1) [54]. In addition, this investigation unlike previous studies will take developmental issues into account. This study will be limited to later adolescence and early young adulthood. In order to enhance scientific generalizability and the actual practice of yoga, it is important to target an age-range that represents similar challenges. For example, older IBS patients will likely have differences in motility, flexibility, and confidence compared to a younger group. A number of reasons underlie the focus on 14-26 year-olds. First, this group is likely to experience similar developmental challenges, including adjustments in a sense of self, family, schooling, and peers [55]. The primary stressors for most young people of this age-range relate to academic and social performance and increasing levels of autonomy. Second, the level of independence during this period will increase retention of subjects. In California, adolescents are able to drive at 16 years of age. Given that attendance will involve transportation considerations, it is likely that independent access to transportation will increase ease of attending the yoga sessions. Third, the target age range reflects the peak in IBS prevalence that remains relatively consistent across adulthood. During high school, IBS rates increase to adult levels of 15%, from around 8% earlier in childhood [3]. This suggests a developmental shift in the illness around adolescence. It is therefore likely that the IBS symptoms experienced by older adolescents will be comparable to those experienced by college-aged young adults. Overall, it is anticipated that the IYP will have similar benefits for adolescents and young adults across the age group studied. Despite the likelihood that IY will prove useful for both adolescents and young adults, consideration will be given to sub-groups within the age-range. It is possible that a 14-26 year-old range crosses important developmental challenges (e.g., entering college), and results will therefore be examined separately for a 14-18 year-old adolescent sub-group and a 19-26 year-old young-adult sub-group. Thus, feasibility, efficacy, and safety will be examined separately for adolescents and young adults, and only if the sub-groups respond similarly to the intervention will final analyses collapse the groups. Such a developmentally-sensitive approach has not been used in yoga research to date.

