### Study participants

#### Enrollment criteria

Male and female youth will be eligible for the study if they meet the following criteria:

• Age 14-26 years.

• Diagnosis of IBS, using ROME III pediatric criteria for patients aged 14-17 years, and ROME III adult criteria for 18-26 year-olds.

• Able and willing to give written informed assent or consent and comply with the requirements of the study protocol.

• Ability to speak and understand English.

Every step will be taken to ensure that equal numbers of participants make up the sub-groups, including equal numbers of young men and women and young people across the entire age group studied.

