#### Sample size determination and power analysis

Based on our previous pilot work using Iyengar yoga for patients with rheumatoid arthritis [82], we estimated that yoga was likely to have a medium effect size on the primary outcomes. For power calculations, a freely-available software for power calculations - G*Power 3- was used to estimate the sample size needed for the estimated effect size using a pre/post by group interaction. Pairing a medium effect size with a range of correlation values (.10 to .50) for baseline and follow-up scores resulted in power calculations ranging from 60 to 34 total subjects. These calculations used a Type I error rate of α = .05, and statistical power of 0.80 (the Type II error rate, 1- β). We settled upon the middle value of 47 total subjects. Assuming a 20% attrition rate, it was estimated that 60 total subjects would need to be recruited (30 per group).

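### The final analysis pools the age groups only if they look alike, a rule that inflates error and that this sample cannot support; the age cuts also disagree between sections

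*Protocol article*

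**What the plan says.** The rule appears twice. Under Data analyses: "Each stage of data analysis detailed below will be carried out separately for adolescent (14-18 yrs) and young adult (19-26 yrs) sub-groups", followed by "If no differences are found, the groups will be combined". Under Yoga as treatment for IBS, on feasibility, efficacy and safety: "only if the sub-groups respond similarly to the intervention will final analyses collapse the groups". Neither place names the test, threshold or outcome that would establish a difference, or says what the trial concludes if one appears. Data analyses itself expects no age differences.

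The sample size section addresses only the pooled pre/post by group test: "we estimated that yoga was likely to have a medium effect size on the primary outcomes" and "These calculations used a Type I error rate of α = .05, and statistical power of 0.80". It gives 60 to 34 subjects across the correlations considered, settles on 47, and recruits 60 to allow for 20% attrition.

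The age boundary varies by section. Enrollment criteria applies "ROME III pediatric criteria for patients aged 14-17 years, and ROME III adult criteria for 18-26 year-olds". Primary outcomes gives the CSI sub-scale, as an addition, to those younger than 18. Psychospiritual functioning states: "Children under 18 years will be administered the Revised Child Anxiety and Depression Scale". The impact of IBS describes the child Rome criteria as covering ages 4 to 18 and the adult criteria as covering those over 18, which matches the 14-18/19-26 analysis split.

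**The concern.** A pooling rule that depends on the observed sub-group results has three costs. First, a non-significant age difference in cells of about 12 is weak evidence that the ages respond alike, yet the article relies on it to show that findings generalise across ages. Second, it gives the trial more than one route to a positive claim on each outcome, so the nominal 5% no longer holds. Third, a chance difference removes the only analysis the trial was sized for and leaves two small ones. The rule covers every stage of analysis, so all the efficacy hypotheses are exposed.

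The age boundary is a separate and smaller matter. If eligibility criteria and some instruments change at 18 but the analysis groups change at 19, the 14-18 group is not homogeneous in how it was diagnosed or, for some measures, in what was measured.

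**Working it through.** **Inputs.** From the sample size section: alpha .05, power .80, "Pairing a medium effect size with a range of correlation values (.10 to .50) for baseline and follow-up scores", N of 60 to 34, 47 chosen, 20% attrition, 60 recruited at 30 per arm. Completers: 60 × 0.8 = 48. Assumptions: two-sided tests; a medium effect is f = 0.25 (0.5 SD is shown as the alternative); equal age split, which Enrollment criteria says is intended, so 24 completers per age group and 12 per arm-by-age cell; independent participants.

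**1. Reproducing the plan's figure.** For the within-between interaction with 2 groups and m = 2 occasions, the noncentrality is λ = f²·N·m/(1−ρ) = 0.125·N/(1−ρ), with 1 and N−2 df.

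| ρ | N | λ | Power |
|---|---|---|---|
| .1 | 60 | 0.125×60/0.9 = 8.33 | 81.0% |
| .3 | 46 | 0.125×46/0.7 = 8.21 | 80.0% |
| .5 | 34 | 0.125×34/0.5 = 8.50 | 80.7% |

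The range 60 to 34 is reproduced, and its midpoint is (60+34)/2 = 47. Attrition gives 47/0.8 = 58.75, so 59 against the stated 60. In a difference-in-change model λ = Δ²·N/[8(1−ρ)], so f = 0.25 means Δ = 1.0 SD.

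**2. Power on that scale with 48 completers.** Pooled: λ = 6/(1−ρ). One age group (24): λ = 3/(1−ρ). Age-by-treatment test for an age difference equal to the whole effect (1.0 SD): λ = 1.5/(1−ρ), a quarter of the pooled value.

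| ρ | Pooled | One age group | Age difference = whole effect | Half that difference |
|---|---|---|---|---|
| .1 | 71.5% | 41.5% | 24.4% | 9.7% |
| .3 | 81.8% | 50.8% | 29.9% | 11.0% |
| .5 | 92.4% | 64.9% | 39.5% | 13.5% |

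**3. Power by ANCOVA, the planned method.** The standard error of the age-by-treatment contrast is √(1−ρ²)·√(4/12). At ρ = .3 this is 0.954 × 0.577 = 0.551, so a 0.5 SD difference has noncentrality 0.5/0.551 = 0.91 and power 14.4%. Over ρ = 0 to .5, power is 13.5-16.5% for 0.5 SD and 39.5-49.8% for 1.0 SD. For a treatment effect of 0.5 SD at ρ = .3, one age group has 23.2% power and the pooled sample 42.7%.

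**4. False-claim rate per outcome, no true effect** (200,000 simulated trials, normal outcome, four equal cells, 48 or 60 participants). Unconditional pooling gives 5%.
- Split if the interaction is significant; claim if either sub-group is then significant: 7.8-8.0%. As a check, pooling followed by a false positive contributes about .95 × .05 = 4.75%; the rest comes from the split branch.
- Split if one sub-group is significant and the other is not: 11.3-11.5%. Such discordance alone occurs in about 2 × .05 × .95 = 9.5% of trials.

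Under the second reading, with an identical true effect of 0.5 SD at both ages, the sub-groups look different by chance in 34% (48 participants) to 39% (60) of trials.

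**5. Age boundaries side by side.**

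| Section | Boundary |
|---|---|
| Data analyses | 14-18 / 19-26 |
| The impact of IBS (Rome criteria) | 4-18 / over 18 |
| Enrollment criteria (Rome III) | 14-17 / 18-26 |
| Primary outcomes (CSI) | under 18 only |
| Psychospiritual functioning (RCADS) | under 18 |

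The 14-18 analysis group thus contains 18-year-olds admitted on adult criteria and without the CSI. If the RCADS replaces the BSI-18 under 18, it also contains two mood scales. The IBS-SSS, Abdominal Pain Index, GIS and SF-36 have no age split.

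**The case against.** The rule is disclosed in advance, has a stated developmental rationale, and sits in a trial that calls itself preliminary and exploratory. An analysis plan could define the test and threshold. Under the milder reading, the inflation from 5% to about 8% is real but modest. The 11% and 34-39% figures rest on a reading that the article does not state. All this is fair and limits the size of the problem. But a threshold set elsewhere would not cure a rule that lets the sub-group results choose the final analysis.

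A reader might call the age comparison nearly powerless throughout, or say the sub-groups cannot detect the planned effect. Neither holds without qualification. On the 1.0 SD effect that reproduces the sample size, a 12-versus-12 ANCOVA has 65-77% power (ρ .1 to .5). The age-by-treatment test reaches 71-92% in the extreme case where one age group has twice the average effect and the other none.

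A reader might also infer that the 18/19 cut gives 18-year-olds the wrong instruments, that it is plainly misplaced, or that mood cannot be analysed. The analysis cut assigns no instrument; 18-year-olds get what the under-18 rules give them. The Rome age ranges in the introduction support that cut. The article does not say that the RCADS replaces the BSI-18, although that is the likelier reading, and both scales cover anxiety and depression. How to combine them may be left to an analysis plan.

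**Conclusion.** The conditional pooling rule is a genuine fault in stated text. With about 48 completers, the age comparison that decides pooling has about 14-17% power for a 0.5 SD difference and 24-40% for one equal to the whole effect at f = 0.25. The false-claim rate per outcome rises from 5% to about 8%, or about 11% under the looser reading. If the groups are split, power falls from 71.5-92.4% to 41.5-64.9%. These figures assume an equal age split, f = 0.25 or 0.5 SD for a medium effect, and no clustering by class. An uneven split would lower the power of the age comparison further.

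The age-boundary mismatch is a separate inconsistency, confined to eligibility criteria, the supplementary CSI and mood. It does not show that participants are measured wrongly, and it leaves the IBS-SSS, Abdominal Pain Index, GIS and SF-36 untouched.

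**What to change.** Make the pooled ANCOVA the main analysis unconditionally, with age group as a covariate. Report the group-by-age interaction with its 95% confidence interval, and both sub-group estimates, as exploratory whatever they show. Delete the condition "If no differences are found, the groups will be combined" and its counterpart in Yoga as treatment for IBS. The order of the completer and intent-to-treat analyses need not change for this point.

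Reconcile the age boundaries in The impact of IBS, Enrollment criteria, Primary outcomes, Psychospiritual functioning and Data analyses, and state whether under-18s complete the RCADS instead of the BSI-18 or in addition to it. Which boundary to adopt is for the investigators.

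The cost is wording only, with no change to recruitment or assessments. Since the article already expects no age differences, little is lost.
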